**Diagnosis**		
	H65	Nonsuppurative otitis media
	H66	Suppurative and unspecified otitis media
	H72	Perforation of tympanic membrane
**Procedure**		
	41527-00	Myringoplasty, transcanal approach
	41530-00	Myringoplasty postaural or endaural approach
	41533-01	Myringoplasty with atticotomy
	41542-00	Myringoplasty with ossicular chain reconstruction
	41551-00	Mastoidectomy by intact canal wall technique with myringoplasty
	41554-00	Mastoidectomy by intact canal wall technique with myringoplasty and ossicular chain reconstruction
	41560-00	Modified radical mastoidectomy with myringoplasty
	41560-01	Radical mastoidectomy with myringoplasty
	41563-00	Modified radical mastoidectomy with myringoplasty and ossicular chain reconstruction
	41563-01	Radical mastoidectomy with myringoplasty and ossicular chain reconstruction
	41626-00	Myringotomy, unilateral
	41626-01	Myringotomy, bilateral
	41632-00	Myringotomy with insertion of tube, unilateral
	41632-01	Myringotomy with insertion of tube, bilateral
	41635-01	Excision of lesion of middle ear with myringoplasty
	41638-01	Excision of lesion of middle ear with myringoplasty and ossicular chain reconstruction
	41789-00	Tonsillectomy without adenoidectomy
	41789-01	Tonsillectomy with adenoidectomy
	41801-00	Adenoidectomy without tonsillectomy
	90114-00	Other procedures on eardrum or middle ear

^a^International Classification, 10th Revision-Australian Modification.

### Dependent Variables

For this study, the term “hearing loss” (HL) is used for a single ear to refer to a certain degree of loss of hearing ability, whereas “hearing impairment” (HI) is used for an individual’s state of hearing loss in both ears. The dependent variables used across all component studies will be HI, and its values will be derived from the hearing assessment data contained in the RHA dataset. It will be an ordinal variable comprising the following categories:

Normal hearing: normal audiometry results in both ears.Unilateral hearing loss: normal in one ear and any degree of hearing loss in the other.Mild HI: mild hearing loss in the better hearing ear.Moderate-or-worse HI: moderate-or-worse hearing loss in the better hearing ear.

Although OM tends to develop early in life in NT Aboriginal children and be persistent and often asymptomatic [19,21], a child may not have a hearing assessment until the child is older, when both the diagnosis of OM and hearing assessment become easier. As a result, a proportion of children may not be tested until after the outcome event for the study. There are also a proportion of children with multiple records of hearing assessment in the RHA database. For the purpose of this study, we assume the results for the first hearing assessment of a child, at any age, are representative of the long-term hearing level for that child.

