## Introduction

### Background

Children’s experiences during infancy and early childhood are critical to their health and educational and socioemotional well-being throughout their life course [1-5]. Through this period of rapid development, children are particularly sensitive to influences from their living environment [1,6]. At this age, the ability to hear is crucial to children’s normal development, as children learn to speak and communicate by imitating the sounds they hear, and hearing impairment (HI) is likely to reduce children’s exposure to sounds and voices and hamper their language development [7]. Consequently, delayed or impaired language learning can adversely affect children’s physical health, as well as social and emotional development [7-9].

Otitis media (OM) and the associated HI among Australian Aboriginal children has been extensively researched [10-19]. Community surveys conducted in Aboriginal children living in remote communities have consistently reported extremely high prevalence of OM, as high as 90% in some reports, which has persisted through decades of clinical and public health interventions [14,18-20]. Studies have also found that OM affects Aboriginal children early in life, is more severe, and persists for longer [7,10,21], with prevalence peaking at the young age of 5 to 9 months [15]. Among the affected children, if OM is left untreated or not treated adequately, it often progresses to chronic suppurative OM (CSOM) and tympanic membrane perforation, with mild to moderate conductive hearing loss [22-24]. The impact of HI on language development may be compounded in Aboriginal children, when English is a second or third language, but school-based teaching relies on English [22,25-28]. In this setting, it may be reasonably expected that OM-related HI may directly or indirectly impact children’s readiness for school and subsequent participation and performance at school, as well as their ongoing social and behavioral development through childhood and adolescence.

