### Remote Hearing Assessment Dataset

The Remote Hearing Assessment (RHA) dataset contains middle ear examination and audiometric assessment information collected by the NT Outreach Hearing Health Program [58]. This program is an Australian Government funded specialist ear and hearing health outreach service, available to all NT Aboriginal children and young people, aged under 21 years, most of whom live in remote communities.

The NT Outreach Hearing Health Program uses pure tone audiometry to assess children’s hearing ability and determine the type (sensorineural, conductive, mixed, or indeterminate) and level of hearing loss. The level of hearing loss of an ear is calculated by taking the average of the thresholds of hearing (as deviation from normal threshold, in decibels Hearing Level—dB HL) for 3 frequencies: 500 Hz, 1000 Hz, and 2000 Hz. The results for each ear are classified as either normal or 1 of 4 ordinal categories of hearing loss, namely mild (16-30 dB HL), moderate (31-60 dB HL), severe (61-90 dB HL), and profound (91 dB HL or greater). This relatively conservative classification of hearing loss was chosen over the more widely used World Health Organization classification, as it is deemed more suitable for children aged under 15 years [58,59]. Further details on this classification of hearing loss are available elsewhere [58]. The clinical assessment for each ear is also recorded and classified under the following categories: acute OM (AOM), AOM with perforation, CSOM, dry perforation, Eustachian tube dysfunction, increase in middle ear pressure, OME, normal, and others.

The dataset provided to this study includes information collected from 2007 to 2015, for over 8000 children and young people aged between 0 and 21 years, which is about 22% of the NT Aboriginal population in this age group. Children and young people access these services through referral by primary care services. From January 2013, access to these services was prioritized according to clients’ need for service. This means that the children and young people whose records are captured in the RHA dataset are not a random sample of the general population, and the information is likely to be biased toward those with abnormal middle ear examination and hearing difficulties.

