### Control Variables

The selection of control variables will vary between studies and the availability of the relevant variables in the linked datasets. We will draw reference from published literature in selecting control variables known to have confounding or moderating effects on the association being investigated. Individual-level control variables will be retrieved from the linked health, education, child protection, and justice datasets, including maternal and perinatal factors from the Perinatal Registry dataset (a statutory collection containing information for all births in the NT), as well as hospital admission diagnoses from the NT Hospital Separation Dataset. Community-level factors will include relative level of geographic remoteness (as measured with ARIA+), housing crowdedness (as measured with average household size and average persons per bedroom in the community), and socioeconomic disadvantage (as measured with the Index of Relative Socio-Economic Disadvantage) [48,50,64]. Aggregated data on these factors will be combined with the linked administrative datasets, using the relevant location variable for each study (either community of residence or school location).

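### First hearing tests taken at widely different ages are pooled into one hearing impairment variable, and neither test age nor birth cohort is a named control

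*Protocol article*

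**What the plan says.** In the protocol article, Dependent Variables fixes the exposure by rule: "we assume the results for the first hearing assessment of a child, at any age, are representative of the long-term hearing level". The same paragraph explains that "a child may not have a hearing assessment until the child is older, when both the diagnosis of OM and hearing assessment become easier", and that "a proportion of children may not be tested until after the outcome event for the study". It also notes that some children have several assessments. The authors' grounds for the rule are that otitis media (OM) in this population starts early and tends to persist.

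Remote Hearing Assessment Dataset gives the source as "information collected from 2007 to 2015", "for over 8000 children and young people aged between 0 and 21 years". Background describes OM as age-dependent, "with prevalence peaking at the young age of 5 to 9 months".

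On adjustment, Control Variables says that "Individual-level control variables will be retrieved from the linked health, education, child protection, and justice datasets", gives perinatal factors and admission diagnoses as examples, adds community-level factors, and lets the selection vary by component study. The Abstract gives a similar list. The Statistical Analysis Plan section adds school fixed effects for attendance and NAPLAN, a univariate screen at P<.25, all two-way interactions among the candidates, and forced retention of key confounders known from past studies. None of these places names age at the hearing test, birth cohort or outcome year.

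**The concern.** The HI category is compared across children as though a result meant the same thing at every test age. A normal first test at 4 and a normal first test at 12 need not reflect the same early hearing. A child whose early loss resolved before a late first test joins the normal-hearing reference group.

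Test age also carries cohort and calendar differences, because one fixed testing window is crossed with outcome windows of different length. If test age is related both to the measured HI category and to the outcome, the contrast with normal hearing partly measures when children were tested. A real effect could then be hidden or a false one created. The article describes no check of the long-term assumption, although some children have repeat assessments.

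**Working it through.** The article states no sample size, effect size or SD, so there is no figure of its own to reproduce.

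**1. Which test ages are possible?** Birth years follow from each outcome window and the approximate outcome age given under Outcome Measures. The lowest test age is max(0, 2007 − latest birth year). The highest is min(21, 2015 − earliest birth year).

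| Component | Outcome data, age | Birth years | Possible test age |
|---|---|---|---|
| AEDC | 2009, 2012, 2015; about 5 | 2004-2010 | 0 to 2015−2004 = 11 |
| Year 1 attendance | 2005-2016; 6-7 | 1998-2010 | 0 to 2015−1998 = 17 |
| Year 3 NAPLAN | 2008-2016; about 8 | 2000-2008 | 0 to 2015−2000 = 15 |
| Maltreatment | 1999-2017, from birth | 1999-2015 | 0 to 2015−1999 = 16 |
| Youth offending | 1997-2017, from age 10 | 1987-2007 | 0 to 21 (dataset limit) |

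These are calendar limits, not observed distributions.

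**2. How closely is test age tied to cohort?**

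- AEDC: the 2009 census (births about 2004) allows tests at 3-11 years, 2012 (births about 2007) at 0-8, and 2015 (births about 2010) at 0-5.
- Attendance: Year 1 in 2005 (births 1998-1999) allows tests only from 2007−1999 = 8 to 2015−1998 = 17 years, always after the outcome. Year 1 in 2016 (births 2009-2010) allows tests only up to 2015−2009 = 6. The two ranges do not overlap, yet both groups enter the same HI categories.

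School fixed effects compare children within a school, so they do not remove cohort differences.

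**3. How large could the bias be?** All inputs here are assumptions: test age uniform on 3-12 years, no true HI effect, outcome SD 1, log-odds of measured HI falling by g per year of later testing, and outcome falling by b SD per year of later testing. To first order, HI and non-HI children differ in mean test age by g × Var(test age), with Var = 9²/12 = 6.75. The spurious difference is therefore about b × g × 6.75. A simulation of 400,000 children gave:

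| g | b | b × g × 6.75 | Without test age | With test age |
|---|---|---|---|---|
| 0.1 | 0.03 | 0.020 | 0.018 | −0.002 |
| 0.1 | 0.06 | 0.041 | 0.041 | 0.000 |
| 0.2 | 0.03 | 0.041 | 0.039 | 0.000 |
| 0.2 | 0.06 | 0.081 | 0.081 | 0.003 |

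With g = 0 or b = 0, the unadjusted difference was within 0.002 of zero. With the signs used here, the HI group looks better than it is, which would mask harm. Reversing one slope reverses the sign.

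**4. Would the P<.25 screen select test age?** Assume 2000 children, SD 1 and a slope of 0.03-0.08 SD per year. The slope's standard error is 1/(√2000 × SD of test age), and the two-sided cut-off is z = 1.15.

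- Ages 2-8: SD = 6/√12 = 1.73 and SE = 0.0129. A slope of 0.03 gives z = 2.32 and selection probability Φ(2.32 − 1.15) = 88%. A slope of 0.08 gives more than 99.9%.
- Ages 2-14: SD = 3.46 and SE = 0.0065. A slope of 0.03 gives z = 4.65 and more than 99.9%.

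The screen would therefore usually keep test age, provided that it is offered as a candidate.

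**The case against.** The strongest reply is that the control list is open. Controls vary by component, key confounders are retained without being listed, and further inclusion criteria, which could include a test-age window, are left to each study. A condensed article need not list every covariate. Step 4 adds that the screen would usually catch test age once it is a candidate, and the two-way interaction step would then examine HI by test age. This stands: a reader might infer that test age could enter only by chance, and that is wrong.

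It does not answer the whole point. The pooling rule is stated, not omitted. Controls are to be chosen from published literature, yet Background says that most earlier studies used clinical OM diagnoses and not a hearing assessment. Such a search may well miss age at audiometry, which is a feature of this dataset.

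A second reply is that the long-term level is openly called an assumption, and that Discussion commits each study to discussing bias. That is fair. However, the examples given are selection into the dataset and complete-case analysis. Test timing is not among them, and discussion does not test the assumption.

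A third reply concerns the remedy, and it also stands. A test-age covariate cannot reclassify a child whose early loss resolved before a late normal test. In Cox models timed from birth or age 10, test age entered at time zero conditions on information that may arise after the event.

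**Conclusion.** The point holds as a gap around a stated rule. First tests from a wide span of ages are treated as equivalent, the data windows tie test age to cohort, neither is a named control, and no check of the equivalence is described. Bias is possible in either direction. The figure of about 0.02-0.08 SD rests wholly on the assumed slopes and age distribution, and it falls to about zero if test age is unrelated to HI or to the outcome.

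Three stronger readings are tempting but not supported:

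- That test ages run from 0 to 21 in every component. That is the range of the whole dataset; by the date arithmetic, only the youth offending study can reach 21.
- That the reason for testing changes with age. The documented change in access is by date, from January 2013.
- That the HI effects are confounded. The article gives no data on how test age relates to HI or to any outcome, so the most that can be said is that they may be.

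**What to change.** In Control Variables and the Statistical Analysis Plan section:

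- Retain age at first test (flexible form, such as a restricted cubic spline) together with birth cohort or outcome year in the AEDC, attendance and NAPLAN models, exempt from the P<.25 screen.
- Prespecify one HI by age-at-test contrast, earlier versus later first test, as a check of the assumption that the first result represents long-term hearing.
- Add a sensitivity analysis limited to tests before the outcome. This addresses timing directly, which the covariate alone does not.
- In the maltreatment and youth offending Cox models, do not enter test age as an unconditional time-zero covariate. Use it in a sensitivity analysis limited to children tested before the event, with follow-up starting at the test, or at age 10 if later for youth offending.

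The cost is plan wording, a few degrees of freedom and smaller numbers in the sensitivity analyses. For example, every child in Year 1 in 2005 or 2006 drops out of the tested-before-outcome analysis, because tests begin in 2007. The test date and date of birth are already needed to identify the first test and to time follow-up.

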**Methods:**

Individual-level information linked across multiple administrative datasets will be used to conduct a series of retrospective observational studies on selected developmental and school outcomes. The predictor variables for all studies are the results from audiometric hearing assessments. The outcome measures are as follows: Australian Early Development Census results, representing developmental readiness for school, assessed around 5 years of age; Year 1 school attendance rates; Year 3 school-based academic performance, assessed in the National Assessment Program—Literacy and Numeracy; incidence of child maltreatment events (including both notifications and substantiated cases); and incidence of a first guilty verdict for youth offenders. Confounding and moderating factors available for the analysis include both community-level factors (including school fixed effects, socioeconomic status, level of remoteness, and housing crowdedness) and individual-level factors (including maternal and perinatal health and hospital admissions in early childhood).

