### Design and Linkage Process

The HeLoKids Project will be conducted as a series of retrospective observational cohort studies to examine the association between HI and a range of developmental, educational, and social outcomes. These studies will utilize administrative datasets held within an extensive repository of deidentified unit-level information for NT children, which has been incrementally developed since 2009 [56]. SA NT DataLink (a South Australia [SA] and NT partnership) [57] completed the linkage of datasets collated in the repository. The data linkage process involves individual data custodians preparing a dataset containing identifying information only and then forwarding the dataset to SA NT DataLink. SA NT DataLink then combines the datasets from multiple custodians and links records for the same individual, which are present in the various datasets, and creates an anonymized project-specific linkage key for each individual. SA NT DataLink then adds the linkage key to the original datasets and returns each dataset to the respective data custodian. The data custodian creates a research dataset by combining the linkage keys with approved research variables and removing identifying information. The research dataset, created by each custodian, is then forwarded to the research team. The research team is able to use the linkage keys to merge information on individuals from multiple datasets to create the datasets necessary for analysis.

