#### School Attendance in Year 1 of Primary School

The outcome measure for this component will be children’s annual school attendance rate for Year 1 (aged approximately 6-7 years). Year 1 is chosen, as it is the first year of compulsory school attendance in the NT and as, in the study population, school attendance rates decrease with increasing year level. The data source will be the School Attendance dataset, provided by the NT Department of Education, which contains records of enrollment and daily attendance status for students studying in NT Government schools for the period 2005 to 2016. The school attendance outcome will be expressed as the number of school days attended per year, with approximately 200 school days available per year.

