#### Youth Offending

The Youth Justice dataset was provided by the NT Department of the Attorney-General and Justice, and this contains records of youth offending in the NT. The outcome measure for this study will be the cumulative incidence of first episode of a proven guilty offence within the youth justice system. The starting point for follow-up will be the 10th birthday, which is the minimum legal age of criminal responsibility, and the follow-up time will be calculated to the date of first offence or censored at the date of death, the last observed date in the linked datasets, or the set endpoint for follow-up of this study. Data are available for the period 1997 to 2017.

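### Hearing status is taken from the first test at any age, possibly after the outcome, and the article states no analysis that checks whether this matters

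*Protocol article*

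**What the plan says.** Under Dependent Variables, the protocol article accepts that some children are first tested late: "As a result, a proportion of children may not be tested until after the outcome event for the study". It then fixes the exposure for everyone: "we assume the results for the first hearing assessment of a child, at any age, are representative of the long-term hearing level". The rule covers the whole project: "The dependent variables used across all component studies will be HI". Calling HI a dependent variable is a labelling slip, since the abstract says "The predictor variables for all studies are the results from audiometric hearing assessments".

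The other relevant facts are these:

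- **Design.** The project "will be conducted as a series of retrospective observational cohort studies" (Design and Linkage Process).
- **Hearing data.** "The dataset provided to this study includes information collected from 2007 to 2015" (Remote Hearing Assessment Dataset). Access is by primary care referral, with priority by need from January 2013.
- **Attendance data.** The source holds "records of enrollment and daily attendance status for students studying in NT Government schools for the period 2005 to 2016".
- **Time origins.** Maltreatment time runs from birth. For offending, "The starting point for follow-up will be the 10th birthday".
- **Bias.** Principal Findings promises a discussion of bias and its likely direction in each component. Its two examples are non-random sampling and complete-case analysis.

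The article states no requirement that the test precede the outcome, no delayed entry, and no analysis by test timing.

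**The concern.** In a cohort study the exposure should describe the child before the outcome, or there should be evidence that a later measurement stands in for the earlier state. Here one test at any age does that work, and two problems follow.

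1. **Misclassification.** A first test at 10 or 12 may not show how the child heard at 5, 6 or 8. The article's own exclusion rule points this way. Children with OM surgery before age 4 are removed because surgery could change the impact of HI. A child operated on at 5 and first tested as normal at 8 stays in, and counts as normal hearing for the age-5 AEDC.
2. **Dependent testing.** Entry to the cohort requires a hearing result, and results arise through referral and need. If factors linked to the outcome also affect whether or when a child is tested, the association can be distorted.

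Both apply to all five hypotheses, and the same variable enters the final structural equation model. The article intends the results to inform policy and resource allocation.

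**Working it through.** The article gives no proportion tested late, no ages at first test and no event counts, so there is no figure of its own to reproduce. What can be checked is whether the data windows allow late tests, and how far assumed inputs could move a result.

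**Step 1: calendar windows.** Testing runs from the start of 2007 to the end of 2015, which is 9 years. For an outcome at time t, the share of the window after it is (2016 − t)/9, bounded to 0 and 1. Mid-year dates for AEDC and NAPLAN, and end of year for attendance, are assumptions.

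| Outcome | Year | Calculation | Share after outcome |
|---|---|---|---|
| AEDC | 2009 | (2016 − 2009.5)/9 | 72% |
| AEDC | 2012 | (2016 − 2012.5)/9 | 39% |
| AEDC | 2015 | (2016 − 2015.5)/9 | 6% |
| Year 1 attendance | 2005, 2006 | 10/9 (bounded), 9/9 | 100% |
| Year 1 attendance | 2009 | (2016 − 2010)/9 | 67% |
| Year 1 attendance | 2012 | (2016 − 2013)/9 | 33% |
| Year 1 attendance | 2015, 2016 | bounded at 0 | 0% |
| NAPLAN | 2008 | (2016 − 2008.5)/9 | 83% |
| NAPLAN | 2012 | (2016 − 2012.5)/9 | 39% |
| NAPLAN | 2016 | bounded at 0 | 0% |

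Maltreatment data cover 1999 to 2017, and 8 of these 19 years (1999 to 2006) precede any possible test. Youth justice data cover 1997 to 2017, and 10 of these 21 years (1997 to 2006) do. Late tests are therefore possible in all five components. These are shares of calendar time, not of children.

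**Step 2: dilution, assumed inputs.** Let q be the share of children tested after the outcome and r the fraction of the true contrast that a late test retains. Observed/true = (1 − q) + q × r.

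- q = 0.1, r = 0.9: 0.90 + 0.09 = 0.99
- q = 0.5, r = 0.5: 0.50 + 0.25 = 0.75

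**Step 3: late results that depend on the outcome, assumed inputs.** Suppose there is no true association, HI prevalence is 50%, and among late-tested children those with the outcome are d more likely to show HI. Then p1 = 0.5 + qd/2, p0 = 0.5 − qd/2, and the odds ratio is [p1/(1 − p1)] / [p0/(1 − p0)].

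- q = 0.1, d = 0.1: (0.505/0.495)² = 1.04
- q = 0.5, d = 0.2: (0.55/0.45)² = 1.49

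**Step 4: selection into testing, assumed inputs.** Suppose children without the event are tested with probability 0.35 if they have HI and 0.15 if not. The cohort odds ratio is multiplied by (testing ratio, event to no event, with HI) / (the same ratio with normal hearing).

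- Event raises testing to 0.50 in both groups: (0.50/0.35)/(0.50/0.15) = 0.43
- Event doubles testing in both (0.70 and 0.30): 2/2 = 1.00
- Event doubles it only with HI (0.70 and 0.15): 2/1 = 2.00

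Steps 2 to 4 show that the bias could be absent, downward or upward. They do not estimate it.

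**The case against.** The strongest reply is that the authors saw the problem. They say that late testing may occur, label persistence as an assumption, and give a reason: OM in this population starts early, lasts and is often silent. They also note that assessment is easier in older children, so a late test is not necessarily the worse one. Each component may add its own inclusion criteria, and the article is a condensed account. All of this stands, and it makes the choice a reasoned one. It does not make it a tested one: the article itself fixes the exposure rule and both Cox time origins, and it mentions repeat records without using them.

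Several stronger readings are tempting but not supported:

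- **That part of every analysis does use post-outcome tests.** The text says only that this may happen, and gives no proportion. The attendance years are the span of the source data, not a stated cohort range.
- **That a notification, poor school result or court contact triggers the test.** The article describes primary care referral and priority by need, and expects bias toward abnormal ears and hearing difficulty. It mentions no child-protection, school or justice route.
- **That maltreatment follow-up starts before any test could exist in 21 of 30 birth years (1986 to 2006).** Maltreatment data begin in 1999, so among birth years observable from birth (1999 to 2015) the count is 8 of 17. Even there, follow-up starting early does not mean that the event came before the test.
- **That the primary analysis must change.** Requiring audiometry before about age 5 could leave an unusual group of children tested young. Delayed entry drops every earlier event and changes the estimand. That trade-off is open to debate.

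**Conclusion.** The concern holds in a limited form. The exposure rule allows hearing to be measured after the outcome in every component, and makes this certain for any included Year 1 child of 2005 or 2006. In the survival models it assigns a later result to time from birth or the 10th birthday. The rule depends on persistence, which no stated analysis examines; the commitment is to discuss bias, and test timing is not among the examples named.

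No bias figure can be taken from the documents. The ranges above (0.75 to 0.99 of the true contrast; a null odds ratio appearing as 1.04 to 1.49; a selection factor from 0.43 to 2.00) rest wholly on assumed inputs and show only that neither direction can be excluded. A reader might conclude that the results are invalid or biased in a known direction. The documents do not support that, because the true share tested late and the stability of hearing across tests are not given. The gap is worth closing because the data needed appear to be already held.

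**What to change.** Keep the current definition if the authors prefer it as primary, and prespecify the following:

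1. For each component, report how many children were first tested before and after the outcome, with age at first assessment.
2. For AEDC, attendance and NAPLAN, add a sensitivity analysis limited to children with a test before the outcome. In the full sample, include age at assessment and an HI by tested-before/after term.
3. For the Cox models, add a sensitivity analysis with delayed entry at the first assessment (for offending, at the later of that date and the 10th birthday), excluding children with an earlier event and including age at assessment. The before/after term suits outcomes with a fixed date better than the Cox models, where that label depends on the event having occurred.
4. From the repeat records, report agreement between first and later HI category.
5. State that wording about impact will be limited if these results differ from the primary ones.

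The cost is extra analysis text, wider intervals in the restricted analyses, and the loss of events before the test under delayed entry. How much sample is lost cannot be computed from the article. No new data should be needed, since identifying a first assessment implies that assessment dates, or at least their order, are held; the date-based steps need the dates themselves.
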